### Randomization and blinding

Based on a random number generated by SAS (Version 9.3, SAS Institute Inc., Cary, NC, USA), participants will be randomized in a 1:1 ratio to either the auricular plaster group or the sham auricular plaster group. Random numbers are generated by a statistician who is not participating in the trial. The random grouping results are sent to the acupuncturists by message. However, the particular characteristics of auricular plaster therapy make it difficult for acupuncturists to be blinded. Participants do not know which group they belong to. APT will be administered to participants in separate rooms according to their assigned groups. Researchers and statisticians in the trial will be blinded to the grouping scenario.

### Basic treatment regimen

Participants will receive standard rehabilitation training for autism according to the published guidelines (6), including physical activities, rhythm classes, sensory integration classes, discrete unit teaching methods, and natural environment teaching. These rehabilitations will be guided by qualified professionals.

### Interventions

Based upon clinical experience in APT for sleep disorders and characteristics of TCM treatment of sleep disorders in children with ASD, the acupoints of the heart (CO15), Jiaogan (AH6a), Shenmen (TF4), subcortex (AT4), kidney (CO10), and spleen (CO13) are chosen in this study (56). The locations of the auricular points can be found in Table 4 and Figure 2. Both groups will be treated with APT for 30 consecutive days. Before participating in the trial, the acupuncturists qualified as Chinese medicine practitioners have at least 3 years of clinical experience, and successfully passed a relevant test, including auricular point positioning, auricular point duration, and participant attention. The auricular plaster (Heshi MedTech Co., Ltd., Hengshui, Hebei, China) consists of cowherb seeds wrapped in a tape of 0.5 cm ^*^ 0.5 cm. Participants in the sham APT group will only be treated with the same shape as auricular plaster without cowherb seeds. To increase compliance, we also manufacture special auricular plaster, which is covered with cartoon stickers. Acupuncturists will change the auricular plaster application for participants every day. Participants are not allowed to take any therapeutic drugs (e.g., melatonin) for sleep disorders during the study.

**Table 4 T4:** Locations of auricular points.

**Auricular point**	**Location**
Heart (CO15)	Located at the middle of the concha
Jiaogan (AH6a)	Located at the junction of the front end of the lower part of the antihelix and the inner edge of the helix
Shenmen (TF4)	Located at the upper of the posterior third of the triangular fossa
Subcortex (AT4)	Located at the medial side of the antitragus
Kidney (CO10)	Located at the rear of the lower part of the antihelix
Spleen (CO13)	Located at the posterior upper part of the concha

**Figure 2 F2:**
[figure not shown]
Location of auricular acupoints.

#### Auricular plaster group

Based on conventional rehabilitation training for children with ASD, children in the auricular plaster group will be provided with APT. Children themselves or their parents are told to press the auricular plaster three times a day (8 a.m., 2 p.m., half an hour before sleep at night), each point for 30–60 s, so that the auricular point produces an acidic and swollen sensation that can be tolerated by the children.

#### Sham auricular plaster group

Participants will receive a sham APT on the same auricular point location as the APT group. They will not be instructed to press the sham plasters.

### Outcome measurements

#### Primary outcome

The primary outcome is the Children's Sleep Habits Questionnaire (CSHQ) (57), which contains seven items, including bedtime, sleep habits, sleep behavior, night wake, morning wake, daytime sleepiness, and total sleep time, with different items representing different sleep problems. Higher scores indicate a greater problem with sleep (58). The CSHQ will be evaluated at baseline and 10, 20, 30, 60, 90, and 120 days after randomization. Sleep assessment ranges from 1 month prior to baseline, every 10 days in the treatment period, and every 30 days in the follow-up period.

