### Sample size

A multisite case-control study which including 552 sleep problem in two to five children with ASD showed that the mean score of the CSHQ for ASD children was 48.5, and the standard deviation (SD) of CSHQ was 9.7 (62). Another study utilizing scalp acupuncture to treat sleep disorders in children with ASD showed a significant improvement in total CSHQ scores of 38 after treatment (63). Based on these two studies, we assume that the mean CSHQ score of children with ASD after receiving APT treatment is 40, and the SD in the auricular plaster group and sham auricular plaster group was 9.7. Assuming a significance level of 0.05 and a study power of 0.8 with a 10% dropout rate, 44 participants were required for this study, with 22 participants in each group. The sample size was calculated using power analysis and sample size (Version 11.0.7, NCSS, Englewood, New Jersey, USA).

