### Statistical analysis

An analysis of the data will be conducted using SPSS (Version 24, IBM, Armonk, New York, USA). Data will be analyzed on the basis of intention-to-treat (ITT) and per-protocol (PP) analysis. The ITT analysis includes all the participants who received at least one acupuncture treatment and one assessment of the primary outcome. The PP analysis includes participants who complete the trial. Continuous data will be expressed as medians and interquartile ranges. Categorical data will be presented as numbers and percentages. Continuous variables will be compared using the independent-sample *t-*test or the Mann–Whitney *U*-test. Categorical variables will be compared with the chi-squared test or Fisher's exact test. Missing values will be addressed by multiple imputations, having appropriately explored the missingness mechanism and in accordance with good practice. Two-sided *P* < 0.05 will be considered significant.

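### No primary time point is fixed for a CSHQ measured at six post-baseline visits, and the total score is not named as the endpoint

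*Protocol article*

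**What the plan says.** Under Primary outcome, the article states "The primary outcome is the Children's Sleep Habits Questionnaire (CSHQ) (57), which contains seven items", lists those parts, and adds "with different items representing different sleep problems". On timing it says "The CSHQ will be evaluated at baseline and 10, 20, 30, 60, 90, and 120 days after randomization". The same paragraph gives recall windows that differ by phase: one month before baseline, ten days during treatment and thirty days in follow-up. No visit is singled out there, in the abstract or in the study schedule (Table 3). The total score is not named in the outcome definition.

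Under Statistical analysis, "Continuous variables will be compared using the independent-sample" *t*-test or the Mann–Whitney test, and "Two-sided *P* < 0.05 will be considered significant". That section gives no order of testing, no adjustment and no repeated-measures model.

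Under Sample size, the authors cite a study in which "the mean score of the CSHQ for ASD children was 48.5" (SD 9.7) and a scalp-acupuncture study that reported total CSHQ scores. They then write "we assume that the mean CSHQ score of children with ASD after receiving APT treatment is 40", with an SD of 9.7 in both arms. The target is set by "Assuming a significance level of 0.05 and a study power of 0.8 with a 10% dropout rate", giving 22 per group.

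**The concern.** A primary outcome is complete only when the score, the time point and the comparison are all stated. Here only the instrument is. The six visits are not interchangeable: days 10 and 20 fall during treatment, day 30 is its end, and days 60, 90 and 120 show whether an effect lasts. A difference at day 10 and a difference at day 120 would support quite different claims, yet the text allows either to be presented as the primary result.

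Two things are at stake. First, no identified test carries the 5% error rate and the 80% power on which the trial was sized. Second, a reader of the eventual report could not tell from this protocol whether the visit presented as primary was chosen in advance or was the most favourable of six.

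**Working it through.** **1. What the sample size implies.** Inputs from Sample size: mean 40 with active treatment, reference mean 48.5, SD 9.7, alpha 0.05, power 0.80. The text does not say that 48.5 is the sham mean; I take it as such, so the difference is 48.5 − 40 = 8.5.

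- Normal approximation: n per arm = 2 × [9.7 × (1.960 + 0.842) / 8.5]² = 20.4, so 21.
- Two-sided *t*-test (noncentral *t*): 22 per arm, power 81.0%.

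The stated 22 per arm is therefore what one two-group comparison of one score needs before any dropout allowance. With 10% dropout the *t*-test figure becomes 22 / 0.9 = 24.4, so 25 per arm. That shortfall is a separate matter. What counts here is that the calculation covers one test, with no allowance for several visits.

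**2. False-positive risk if any visit may count.** Inputs: six post-baseline visits (Primary outcome) and two-sided 0.05 at each (Statistical analysis). The between-visit correlation is not given and is varied.

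- Independent visits, the upper reference: 1 − 0.95⁶ = 1 − 0.735 = 26.5%.
- Correlated visits: simulated two-sample *t*-tests under no effect, 22 per arm, 40,000 trials per setting. At a rate of 20% the simulation standard error is √(0.2 × 0.8 / 40,000) = 0.2 percentage points.

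| Correlation | Equal between all visits | Decaying with distance between visits (AR(1)) |
|---|---|---|
| 0.3 | 24.0% | not run |
| 0.5 | 20.8% | 23.8% |
| 0.6 | 19.0% | 21.8% |
| 0.7 | 16.7% | 20.5% |
| 0.8 | 14.2% | 17.5% |
| 0.9 | 11.0% | 13.4% |

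With 20 per arm and an equal correlation of 0.6 the result is again 19.0%, so the arm size hardly matters.

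**3. Direction of the error.** These rates count false results in either direction. For independent visits, the chance of at least one false result favouring active treatment is 1 − 0.975⁶ = 14.1%. At correlation 0.9 it is about half of 11.0%, or 5.5%. A single two-sided test at 0.05 gives 2.5%.

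**4. Can all six visits be kept with an adjustment?** Bonferroni would test each visit at 0.05 / 6 = 0.0083 (critical value 2.638). With 22 per arm and a difference of 8.5:

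- Standardised difference: 8.5 / [9.7 × √(2/22)] = 8.5 / 2.925 = 2.906.
- Power at a given visit: Φ(2.906 − 2.638) = Φ(0.268) = 61%, against Φ(2.906 − 1.960) = 83% for one unadjusted test on the same approximation.

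The trial has room for one primary test, not six.

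**The case against.** The strongest reply is that the document already points to one comparison. The sample size rests on a single mean after treatment and cites total scores. The Study design section separates a 30-day treatment period from a 90-day follow-up. Under Secondary outcomes, polysomnography is repeated at the end of treatment. The Discussion says the CSHQ serves to compare sleep problems pre- and post-treatment. Read together, these lean towards the total score at day 30. That is fair, and it is why day 30 is the natural choice. But none of these places fixes a day, days 30, 60, 90 and 120 all come after treatment, and the outcome definition adopts none of them.

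A second reply is that this is a condensed article and that multiplicity methods often sit in an analysis plan, which is not shown. This stands for adjustment methods and testing order, and no fault is found on those. It does not cover the time point, which belongs in the definition of the primary outcome, and the article gives that definition a section of its own.

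Two stronger readings are tempting and not supported. A reader might infer that every visit is planned as a primary test at 0.05. The statistical section is generic and does not say so; it leaves the question open. A reader might also infer that the seven CSHQ parts are separate primary endpoints, which would multiply the tests further. The remark about different sleep problems describes the questionnaire, no section proposes component-level tests, and the sample size uses one score.

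**Conclusion.** The point holds in this form: the primary outcome lacks a fixed time point and an explicit score, and the stated rule does nothing to narrow six visits to one. The risk of 11% to 26.5% is conditional. It applies only if success may be claimed at any visit, and its place in the range depends on a between-visit correlation that the document does not give. Under the patterns examined, even a correlation of 0.9 leaves the risk at more than twice the nominal 5%. That the definition is incomplete is certain from the text; the size of the resulting error is an assumption-based range. This should be settled before unblinding, because it decides what the trial's primary claim is.

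**What to change.** Before unblinding, add to the outcome definition and the statistical section: the primary endpoint is the CSHQ total score at day 30, the end of the 30-day treatment period, compared between groups once at two-sided 0.05. State that the CSHQ at days 10, 20, 60, 90 and 120 and the CSHQ components are secondary and will be reported as estimates with 95% confidence intervals. The ABC and polysomnography are already labelled secondary and need no change.

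This agrees with the treatment period in Study design, the end-of-treatment polysomnography and the single comparison behind the sample size. It costs about two sentences, with no new data and no change to visits or treatment. The small downside is that an effect seen only at another visit could not carry the primary claim.

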#### Secondary outcomes

Secondary outcomes include the following:

1) The polysomnography (PSG) system (Natus Neurology Incorporated, Wisconsin, USA), a clinical measure for evaluating sleep conditions, is considered to be the “gold standard” for determining sleep-related disorders (59). The sleep variables of PSG include the following: total sleep time (TST), sleep latency (SL), awakening duration, and sleep stages (non-rapid eye movement sleep stage 1 (NREM1), NREM2, NREM3, rapid eye movement (REM) sleep latency and REM sleep) (60). Sleep stages are determined by analyzing the electroencephalogram (EEG), electrooculogram (EOG), and chin electromyogram (EMG) recording. EEG derivations F4-M1, C4-M1, and O2-M1 are obtained from the electrical activity in frontal, central, and occipital brain regions. The frequency filter for these derivations ranges from 0.3 to 35 Hz. The EOG derivations E1-M2 and E2-M2 are determined by electrodes placed in the left and right outer canthus, respectively, with frequency filters ranging from 0.35 to 35 Hz. Three electrodes placed at the chin provide the EMG derivations EMG1, EMG2, and EMG3, which have a frequency filter of 10–100 Hz. Children with ASD will receive 16-h PSG monitoring at baseline and the end of treatment. The PSG data will be analyzed by Natus ^®^ SleepWorks™ PSG software. A certified neurosurgeon with 8 years of experience ([name]) who has passed the Chinese PSG technical operation examination will audit the PSG data.2) Autism Behavior Checklist (ABC), which is one of the five components of the Autism Screening Instrument for Educational Planning (61). There are 57 items divided into five parts in the ABC, which are categorized into five areas: sensory, relating, body and object use, language, and social and self-help skills. The ABC follows the same assessment schedule as the CSQH. The CSHQ and ABC questionnaires were assessed by one independent assessor who was blinded to group allocation.

### Sample size

A multisite case-control study which including 552 sleep problem in two to five children with ASD showed that the mean score of the CSHQ for ASD children was 48.5, and the standard deviation (SD) of CSHQ was 9.7 (62). Another study utilizing scalp acupuncture to treat sleep disorders in children with ASD showed a significant improvement in total CSHQ scores of 38 after treatment (63). Based on these two studies, we assume that the mean CSHQ score of children with ASD after receiving APT treatment is 40, and the SD in the auricular plaster group and sham auricular plaster group was 9.7. Assuming a significance level of 0.05 and a study power of 0.8 with a 10% dropout rate, 44 participants were required for this study, with 22 participants in each group. The sample size was calculated using power analysis and sample size (Version 11.0.7, NCSS, Englewood, New Jersey, USA).

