## Methods and analysis

### Study design

This study is a parallel-design, patient-assessor blind randomized controlled trial (RCT) comparing the use of APT with sham APT. The recruitment of participants will take place from 1 August 2021 to 31 December 2022. The program will enroll autistic preschoolers with sleep disorders who will be assessed at the Sichuan Beidouxing Rehabilitation Service Center as well as three other community hospitals (Fuqin Community Health Service Center, Tiaodenghe Community Health Service Center, and Xianqiao Community Health Service Center). The clinical trial was registered on CHiCTR.org.cn (ChiCTR2100048257) before we enrolled our first participant, and the study was approved by the Second Affiliated Hospital of Chengdu Medical College, China National Nuclear Corporation 416 Hospital Ethics Committee (KJ2021012).

Eligible participants will be randomly assigned to the APT group or the sham APT group on a 1:1 basis. An observation period of 120 days will be conducted, including a 30-day treatment period and a 90-day follow-up period. Children will receive APT continuously for 1 month. Assessments will be conducted at baseline as well as 10, 20, 30, 60, 90, and 120 days after randomization. The study flowchart is shown in Figure 1, and the schedule of the trial is shown in Table 3.

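### The sample size states no sham-arm CSHQ mean; its 80% power needs the sham arm to end at about 48.5 or higher, a value taken from an observational study

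*Protocol article*

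**What the plan says.** The Study design section of the protocol article describes a "randomized controlled trial (RCT) comparing the use of APT with sham APT". Of the control arm, the section on the sham group says: "Participants will receive a sham APT on the same auricular point location as the APT group". The Basic treatment regimen section applies to both arms: "Participants will receive standard rehabilitation training for autism according to the published guidelines".

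The Sample size section rests on two outside sources. The first is introduced as "A multisite case-control study which including 552 sleep problem in two to five children with ASD"; it "showed that the mean score of the CSHQ for ASD children was 48.5, and the standard deviation (SD) of CSHQ was 9.7". The second is a scalp acupuncture study that "showed a significant improvement in total CSHQ scores of 38 after treatment". From these the authors write: "we assume that the mean CSHQ score of children with ASD after receiving APT treatment is 40". They set the SD at 9.7 in both groups, the significance level at 0.05, power at 0.8 and dropout at 10%, and arrive at 44 children, 22 per arm. No expected CSHQ mean for the sham group appears. The Statistical analysis section plans an independent-sample t-test or Mann-Whitney U-test with a two-sided 0.05 threshold.

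**The concern.** A two-arm sizing on means needs a difference between the arms, and so a value for each arm at the time of comparison. Here only the active arm has one. If 48.5 fills the gap, a mean observed in children with ASD in a case-control study stands in for the post-treatment mean of an arm that receives sham plaster at the same points plus guided rehabilitation. The article does not argue that such an arm would end at 48.5.

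Power depends directly on this value. Each point by which the sham mean falls below 48.5, with the active arm at 40, takes one point off the difference the trial has to detect. If the margin is thin, the printed power of 0.8 could be well above the real power for active versus sham, and a non-significant result would be read with more confidence than the design earns.

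**Working it through.** **Inputs.** Active mean 40, SD 9.7 in both arms, alpha 0.05, power 0.80, dropout 10%, 22 per arm (all from Sample size); two-sided t-test (Statistical analysis); 1:1 allocation (Randomization and blinding). Candidate sham mean: 48.5, the case-control value.

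**Step 1: reproduce the plan's figure.** Difference = 48.5 − 40 = 8.5 points; 8.5/9.7 = 0.876 SD.

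- Normal approximation: n per arm = 2(1.960 + 0.842)² × 9.7²/8.5² = 20.44, so 21.
- Two-sample t-test (noncentral t, df = 2n − 2, noncentrality = (8.5/9.7)√(n/2)): power is 0.791 at n = 21 and 0.810 at n = 22. The smallest size reaching 80% is 22 per arm, 44 in total.

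This matches the printed number exactly, but before any dropout allowance. With the allowance added after rounding, the t-test size would be 22/0.9 = 24.4, so 25 per arm.

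**Step 2: how firm is the inference of 48.5?** It is the only printed CSHQ mean that can serve as the control and it reproduces 22. The arithmetic alone does not make it unique. An unprinted sham mean of 49 (difference 9) gives 19 per arm by the normal formula, and 19/0.9 = 21.1, so 22 after dropout. That alternative needs a still higher sham mean, so it does not ease the point.

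**Step 3: evaluable numbers.** 22 × 0.9 = 19.8, about 20 per arm.

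**Step 4: difference detectable with 80% power (t-test, SD 9.7).**

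- 22 per arm: 8.4 points, so a sham mean of about 48.4 with the active arm at 40.
- 20 per arm: 8.8 points, so a sham mean of about 48.8.

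**Step 5: power with the active arm at 40.** The article gives no expected sham mean, so the rows below 48.5 are an assumed range.

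| Sham mean | Difference | Power, 20 per arm | Power, 22 per arm (no losses) |
|---|---|---|---|
| 48.5 | 8.5 | 77% | 81% |
| 47.5 | 7.5 | 66% | 71% |
| 46.5 | 6.5 | 54% | 58% |
| 45.5 | 5.5 | 42% | 45% |

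A sham mean 1 point lower, about 0.1 SD (1/9.7), costs about 10 percentage points.

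**The case against.** **The stronger reading goes too far.** A reader might infer that 80% power requires sham children not to improve at all. The article does not support that. Power depends on where the two arms end, not on how far the sham arm moves. No expected baseline is stated for this trial, and the Inclusion criteria admit only children who also meet sleep-disorder criteria. If they start above 48.5, sham children could improve down to 48.5 with power unchanged. This stands, and it is why the point concerns the final sham mean.

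**The make-up of the 8.5 points is unknown.** A reader might also infer that the difference contains placebo response, practitioner contact, rehabilitation effect or regression to the mean. The two source values come from different studies, and the article gives neither study's background care nor the baseline or control arm of the scalp acupuncture study. No such breakdown can be read from it. Nor should the point lean on the questionnaire being parent-reported: the article names no informant and says one blinded, independent assessor administered it.

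**The plan shows some caution.** It uses 40 where its source reports 38. If the active arm did reach 38, a sham mean of 46.5 would still leave 8.5 points. That is fair, but it is caution about the active arm, and the stated calculation uses 40.

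**Baseline adjustment could recover power.** With an assumed baseline correlation of 0.5 and 20 per arm (normal approximation), power would be 89% at a sham mean of 48.5 and 69% at 46.5. The analysis described is an unadjusted two-group test, so this is not credited to the plan.

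**The sham mean may be in a fuller protocol.** It may. But the article prints its inputs and the power it draws from them, and those inputs do not describe the control arm.

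**Conclusion.** The point holds in this limited form. The article gives no sham-arm mean, and its 22 per arm matches the use of an observational 48.5 in that place. The stated 80% power is met only if the sham arm ends at about 48.5 or higher while the active arm reaches 40; allowing for the plan's 10% dropout, the threshold is about 48.8. There is almost no slack below that: 77% at 48.5, then about 66%, 54% and 42% for sham means 1, 2 and 3 points lower.

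These figures assume SD 9.7, an active mean of 40, an unadjusted two-sided t-test at 0.05 and about 20 evaluable children per arm. How low the sham mean will be is not known from the article, so the lower figures are a range and not a forecast. The article already lists the relatively small sample as a limitation but does not quantify it. The matter is one of correcting a stated figure; design and analysis are not invalidated.

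**What to change.** In the Sample size section:

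1. State the CSHQ mean assumed for the sham-plus-rehabilitation arm after treatment, with its basis.
2. Express the sizing assumption as an active-minus-sham difference.
3. Replace the single power of 0.8 with power at evaluable numbers. Suggested wording: With about 20 evaluable children per arm after 10% dropout (SD 9.7, two-sided 0.05, t-test), 80% power requires a difference of about 8.8 points (8.4 if all 22 per arm are retained). With a mean of 40 under active treatment, power is about 77% if the sham mean is 48.5, and about 66%, 54% or 42% if it is 1, 2 or 3 points lower (81%, 71%, 58% and 45% with no losses).
4. Commit to reading a non-significant primary result through its confidence interval, set against that detectable difference, and not as evidence of no effect.

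The change is to wording only, with no extra enrolment and no change to treatment or assessments. The cost is a less favourable stated power.

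### On the inputs printed in the sample-size paragraph, 44 children give 80% power only before dropout; after the stated 10% loss, power is about 77%

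*Protocol article*

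**What the plan says.** The Sample size section takes two external studies as its basis. From a multisite case-control study it reports a result that "showed that the mean score of the CSHQ for ASD children was 48.5", with an SD of 9.7. From a scalp-acupuncture study it reports a post-treatment total score of 38. It then says "we assume that the mean CSHQ score of children with ASD after receiving APT treatment is 40", and that "the SD in the auricular plaster group and sham auricular plaster group was 9.7". The conclusion is: "Assuming a significance level of 0.05 and a study power of 0.8 with a 10% dropout rate, 44 participants were required for this study". Each arm is to have 22.

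The section does not give the mean assumed for the sham arm, the test behind the calculation, its sidedness, or the number per arm before dropout. The Statistical analysis section plans an independent-sample t-test or a Mann–Whitney test for continuous variables and sets the threshold at two-sided P < 0.05. Allocation is 1:1.

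**The concern.** The paragraph presents 44 as a number that already absorbs 10% dropout and still leaves 80% power. With the only untreated CSHQ mean it cites as the comparator, 22 per arm is exactly what the t-test requires with nobody lost. The dropout allowance and the stated power therefore cannot both be met at 44.

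At stake is the accuracy of the power claim. A non-significant result would be read against a stated 80% when the printed assumptions support a somewhat lower figure. The Discussion already lists the small sample as a limitation, so the power attached to that sample should be correct.

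**Working it through.** **Inputs from the Sample size section**
- Mean after auricular plaster therapy: 40
- SD in both arms: 9.7
- Significance level 0.05, power 0.80, dropout 10%
- Stated size: 44, 22 per arm

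**Inputs from elsewhere or assumed**
- Two-sided testing and the t-test: Statistical analysis section
- 1:1 allocation: Randomization and blinding section
- Sham mean 48.5: an assumption, since no sham mean is stated and this is the only untreated figure cited

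**Step 1. Standardised difference.** (48.5 − 40)/9.7 = 8.5/9.7 = 0.876.

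**Step 2. Number per arm before dropout**
- Normal approximation: n = 2(1.960 + 0.842)²/0.876² = 20.4, so 21 per arm.
- Two-sided t-test (noncentral t with 2n − 2 degrees of freedom and noncentrality 8.5/(9.7·√(2/n))): power is 0.791 at n = 21 and 0.810 at n = 22, so 22 per arm.

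The t-test reproduces the stated 22 per arm and 44 in total, with no dropout allowance in it.

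**Step 3. Adding 10% dropout, n/(1 − 0.10)**
- t-test: 22/0.9 = 24.4, so 25 per arm, 50 in total.
- Normal approximation: 21/0.9 = 23.3, so 24 per arm, 48 in total.

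**Step 4. Power left if 44 are randomised and 10% are lost.** 22 × 0.9 = 19.8, about 20 per arm.

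| Evaluable per arm | t-test | Normal approximation |
|---|---|---|
| 22 | 0.810 | 0.828 |
| 20 | 0.770 | 0.791 |
| 19.8 | 0.766 | 0.787 |

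With 20 against 19 evaluable, t-test power is 0.759. At 20 per arm, the difference detectable with 80% power is 8.8 points by the t-test and 8.6 by the normal approximation.

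**Step 5. Other routes to 44**
- One-sided 0.05: 17 per arm, then 17/0.9 = 18.9, so 19 per arm and 38 in total. This does not give 44.
- Normal approximation rounded only at the end: 20.44/0.9 = 22.7, so 23 per arm and 46 in total. Close, but not 44.
- A base rounded down to 20 and multiplied by 1.1: 22 per arm. This gives 44, but 20 evaluable per arm misses 80% under either formula (Step 4).
- A higher sham mean: differences of 9.1 to 9.3 (sham mean 49.1 to 49.3) need 19 per arm by the t-test, and 19/0.9 = 21.1, so 22 per arm and 44 in total. The normal approximation gives the same at a difference of 9 (sham mean 49).

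**The case against.** The strongest objection is that the result turns on an input the article does not state. A sham mean only 0.6 points above 48.5 would make 44 correct with dropout included. This stands as a limit on certainty. It does not rescue the figure as printed: the section says its assumptions come from the two cited studies, and neither is reported with a mean near 49.1 to 49.3.

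A reader might go further and infer that the investigators named the dropout allowance and then forgot to apply it. The documents do not support that. Some inflation may have been applied to a base of about 20 per arm, and nothing printed separates the two explanations. What can be shown is that the result does not follow from the inputs.

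A second objection is that dropouts are not all lost to the analysis. The ITT set keeps every child with at least one treatment and one primary-outcome assessment, the CSHQ is taken at days 10, 20 and 30, and multiple imputation is planned. Some information would be recovered, so 20 per arm is the completers' case. Imputation does not restore all of it, however, and a dropout allowance exists to cover such loss.

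A third objection is size. The gap is about 3 points, and the SD is borrowed: at an SD of 9.3, 20 per arm would give 0.804. This stands, and it limits the severity.

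A reader might also infer that the trial is badly underpowered because sham children could improve. If the sham arm improved by 1.5 or 2.5 points (differences of 7 and 6), power at 20 per arm would be 0.60 or 0.48. The documents give no sham response, so these are illustrative scenarios and carry no weight here.

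**Conclusion.** On the printed inputs, 44 children do not deliver 80% power with a 10% dropout allowance. They give about 81% with no loss and about 77% with 10% loss (79% by the normal approximation). Meeting the claim as written would take 48 to 50.

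This assumes a sham mean of 48.5, two-sided 0.05, the planned t-test, and full loss of information from the children who drop out. The severity is modest: about 3 points of power, 4 to 6 children, or a detectable difference of 8.8 points where 8.5 was planned. It is an error in a stated figure that should be corrected. It does not put the trial's validity in doubt.

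**What to change.** Revise the Sample size paragraph to:
- state the mean assumed for the sham arm and its source;
- name the test and its sidedness, and give the number per arm before dropout;
- if 48.5 is the intended sham mean, say that 44 randomised gives about 81% power with no dropout and about 77% with 10% dropout for 8.5 points (SD 9.7), equivalent to 80% power for about 8.8 points after that loss;
- if another sham mean was used, state it and show how 44 follows.

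The cost is one paragraph and a slightly less favourable power figure. Recruitment is already under way, and the restatement needs no additional children. Raising the total to 48 to 50 is the alternative if 80% after dropout is to be kept.

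Two additions are optional. The paragraph could show power for smaller differences as a sensitivity check. Separately, ANCOVA on the baseline CSHQ, which is already collected, would give about 81% at 20 per arm if the baseline–outcome correlation were 0.3. That correlation is an assumption the documents do not supply, and adopting ANCOVA would also mean changing the Statistical analysis section.
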